### Interpretation Guidance

All findings will be interpreted as preliminary, hypothesis-generating signals requiring confirmation in adequately powered trials. We will report effect sizes, CIs, and descriptive patterns rather than definitive claims of efficacy or lack thereof. The pilot’s value lies in feasibility demonstration and effect size estimation for future sample size calculations, not in definitive answers about intervention effectiveness.

### Data Monitoring Oversight

The researcher monitors study progress, enrollment rates, data quality, and adverse events throughout the study period. No formal data monitoring committee is established, given the pilot scale of the study and the use of a low-risk intervention (behavioral recommendations only).

### Interim Analysis

No formal interim analysis is planned. The researcher conducts data quality monitoring but does not analyze outcomes until study completion to prevent bias.

### Stopping Guidelines

The study may be stopped early if (1) enrollment fails to reach the target within 18 months, (2) 50% of enrolled participants withdraw, (3) serious adverse events attributable to study procedures occur, or (4) unexpected device failures affect >30% of participants.

### Harms: Adverse Event Tracking

The following events are tracked:

Study-related events: documented at 3 interaction points (baseline, day 30, and day 60)Behavioral or environmental factors: captured in the closure interviewWithdrawal events: managed according to informed consent proceduresAll adverse events: recorded and reported in the final analysis

### Behavioral Factor Assessment

The study closure interview captures key behavioral factors affecting sleep (alcohol consumption, exercise, and stress) that may confound the results. Rather than excluding participants with these factors, we document them to understand their impacts on intervention effectiveness. This approach maintains ecological validity while acknowledging potential confounders.

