### Interventions

#### Control Intervention: Generic Sleep Hygiene Education

Control group participants receive standardized sleep hygiene education on day 30, covering general recommendations applicable to all adults. Examples include maintaining a consistent sleep-wake schedule and sleeping between 7 and 9 hours per night. These recommendations are not personalized to individual sleep patterns.

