### Intervention Delivery and Verification

Experimental group participants receive personalized recommendations explained by the researcher in person on day 30. Participants can clarify and provide feedback. A closure interview at day 60 verifies engagement and implementation attempts, and includes a subjective effectiveness assessment.

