### Personalized Sleep Intervention Framework

The intervention content is based on individual ML feature importance ranking, and participants receive nonpharmacological recommendations from a predefined library (Multimedia Appendix 1) targeting their top 2‐4 predictive sleep parameters [108-116]. Example recommendations for TST optimization (if sleep_duration is a key predictor) are as follows: ensure wake-up time commitment for too much sleep and bedtime commitment for too little sleep. Example recommendations for sleep efficiency enhancement (if movement_awakening is a predictor) are as follows: use white noise, ensure a quiet environment, and restrict caffeine intake (avoid intake ≤6 hours before bedtime). Example recommendations for sleep timing regulation (if sleep_cycle is a predictor) are as follows: ensure a consistent sleep-wake schedule and keep the bedroom cool (around 18 °C‐20 °C).

Experimental group participants receive personalized recommendations, and the top 2‐4 recommendations are explained by the researcher during the in-person meeting. Adherence tracking involves self-reported compliance assessed at study closure (0%‐100% scale). Control group participants receive generic sleep hygiene education without personalization by the researcher during the in-person meeting.

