### Exploratory Outcomes

The exploratory outcomes include (1) individual sleep parameter changes (which specific variables improve), (2) adherence to personalized recommendations (self-reported 0%‐100% scale), and (3) behavioral confounders (alcohol consumption, exercise, and stress documented in the closure interview).

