### Statistical Methods

#### Primary Analysis: Single-Covariate Analysis of Covariance

The mean sleep score in the postintervention period (days 31‐60) is compared between groups using analysis of covariance with a single covariate: mean sleep score in the baseline period (days 1‐30).

$$Model:Postintervention\;score=\beta_{0}+\beta_{1}\;(group)+\beta_{2}\;(baseline\;score)+\epsilon$$

The control group is coded as “0,” and the experimental group is coded as “1.” The primary inference is based on the β₁ coefficient (group difference adjusted for baseline). The effect size is calculated as Cohen *d* with 95% CIs. Statistical significance is assessed at *α*=.05 (1-tailed per directional hypothesis), but the interpretation emphasizes the effect size magnitude and CI width, given the pilot nature of the study.

We do not use multiple covariates (age, sex beyond stratification, and behavioral factors) to avoid overfitting with the small sample size. Sex stratification in randomization addresses balance concerns without requiring covariate adjustment.

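### Alcohol, exercise and stress are labelled confounders but recorded only at day 60, after 30 days of advice in both arms, so they cannot serve their stated exploratory purpose

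*Protocol article*

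**What the plan says.** Under Behavioral Factor Assessment the protocol article writes "The study closure interview captures key behavioral factors affecting sleep (alcohol consumption, exercise, and stress) that may confound the results". It adds that participants with these factors are not excluded; instead "we document them to understand their impacts on intervention effectiveness". Exploratory Outcomes lists "behavioral confounders (alcohol consumption, exercise, and stress documented in the closure interview" as its third item. The Harms section also assigns behavioural factors to the closure interview, whereas study-related events are documented at three contacts: baseline, day 30 and day 60.

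Intervention Delivery and Verification fixes the interview date: "A closure interview at day 60 verifies engagement and implementation attempts, and includes a subjective effectiveness assessment". Both arms have been advised by then. For the experimental arm, "Experimental group participants receive personalized recommendations explained by the researcher in person on day 30". For the control arm, "Control group participants receive standardized sleep hygiene education on day 30, covering general recommendations applicable to all adults".

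The primary model leaves these factors out by choice: "We do not use multiple covariates (age, sex beyond stratification, and behavioral factors) to avoid overfitting with the small sample size". Its only covariate is the mean sleep score over days 1-30. The article says that it contains the complete analysis plan and that no separate one exists.

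**The concern.** A confounder or effect modifier of an intervention has to be known as it stood before the intervention could act on it. Here the three factors are recorded 30 days after the advice. The advice is behavioural; the examples given include "use white noise, ensure a quiet environment, and restrict caffeine intake". It is plausible, though not documented, that such advice also shifts drinking, exercise or perceived stress.

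A difference between arms at day 60 could therefore have at least three sources: a chance imbalance present from the start, an effect of the advice, or an unrelated event after day 30. These call for different readings. The first would be a reason to interpret the effect with the imbalance in mind. The second is part of the effect and should not be explained away.

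What is at stake is the pilot's hypothesis generation. Under Pilot Objectives, the article asks whether some subgroups respond better. Subgroups defined by these factors would need values from before the advice.

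**Working it through.** **Timing, from the article**

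| Contact | Listed content | Alcohol, exercise, stress recorded? |
|---|---|---|
| Enrolment | Eligibility screening, usual care patterns | Not named |
| Day 0 | PSQI | Not named |
| Day 30 | PSQI, then advice in both arms | Not named |
| Day 60 | PSQI, closure interview | Yes |

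The weekly medication diary (Concomitant Care Protocol) and the sleep diaries (Data Collection Quality Control) are not said to record them either. The gap from advice to measurement is 60 − 30 = 30 days.

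**How often chance alone produces a visible gap**

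The article gives no figure for this, so there is none to reproduce. The input from the article is 16 per arm. The prevalence is an assumption.

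- Let X and Y be the numbers with the behaviour in each arm, each Bin(16, 0.5). Then X + (16 − Y) is Bin(32, 0.5), so P(|X − Y| ≥ 4) = 2 × P(Bin(32, 0.5) ≤ 12) = 2 × 0.1077 = 0.215. A gap of 4 people is 4/16 = 25 percentage points.
- Summing the product of the two binomial probabilities over all pairs with |X − Y| ≥ 4 gives 0.119 at a prevalence of 20%, 0.175 at 30% and 0.206 at 40%. The 21.5% is thus the top of the range.
- For a continuous factor in SD units, the standard error of the arm difference is √(2/16) = 0.354, and P(|difference| > 0.5 SD) = 2 × [1 − Φ(0.5/0.354)] = 0.157.

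**Why day-60 data cannot tell the cases apart**

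Assume that the factor shifts the sleep score by b = −0.3 to −0.5 per SD, that a stable sleep trait has variance 1, that period noise has variance 0.25, and that there is no other treatment effect. Let the arms differ by 0.5 SD in the factor at day 60.

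| Source of the day-60 difference | Group coefficient, planned model | After adding the day-60 factor |
|---|---|---|
| Present before the advice | 0.5b × 0.25/(1.25 + b²) = −0.03 to −0.04 | 0 |
| Caused by the advice | 0.5b = −0.15 to −0.25 | 0.4b = −0.12 to −0.20 |

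In the first row, adding the factor removes a small residual imbalance, which is right. In the second row, the planned model already gives the correct total effect and adding the factor takes away a fifth of it. The arm difference in the factor is the same 0.5 SD in both rows, so the day-60 measurement does not say which row applies. Adding a pre-advice value instead gives 0 in the first row and leaves −0.15 to −0.25 intact in the second.

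An unrelated change after day 30 gives the same figures as the second row. A pre-advice value would identify prior imbalance, but it would not separate the advice from a coincident outside event.

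**The case against.** A reader might infer that the trial's effect estimate is confounded. The documents do not support that. Arms are randomised, the primary model excludes behavioural factors, and a stable difference in these habits already acts on the days 1-30 score that serves as covariate. In the illustration above, a 0.5 SD pre-existing imbalance leaves only −0.03 to −0.04. This objection stands in full.

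A reader might also infer that the plan will split or adjust the effect by day-60 values and so understate it. None of the three analyses listed under Exploratory Analyses uses these factors, and Behavioral Factor Assessment speaks of documenting and acknowledging them. The attenuation above describes a misuse that the stated purpose invites, not a planned step.

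It is fair, too, that stress, alcohol and exercise vary over time. Exposure during days 31-60 can only be recorded at the end of that period, so the day-60 interview is needed. What is lacking is an earlier measurement beside it.

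Two points limit certainty. The advice examples in the article name none of the three factors, and the full recommendation library is not shown, so an effect on them is plausible but unverified. The interview's questions and recall window are not given, so it might ask about earlier habits. Such recall would still follow the advice. The experimental arm would have known its assignment since day 30, and the same interview collects adherence and perceived effectiveness. That would not restore a clean baseline.

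Finally, all findings are labelled hypothesis-generating. This lowers the severity but does not make the measurement fit its stated purpose.

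**Conclusion.** The point holds for the exploratory use set out under Exploratory Outcomes and Behavioral Factor Assessment, and nowhere else. The factors are named as confounders, yet the only described measurement comes after the intervention, so prior imbalance cannot be told from later change. The chance of a gap of 4 or more people is 21.5% at 50% prevalence and 11.9% at 20%. Both rest on assumed prevalence and on participants being independent. The coefficients in the illustration rest on assumed effects of −0.3 to −0.5 per SD and serve only to show direction. The primary comparison is not biased by this. Severity is minor.

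**What to change.** Keep the day-60 questions, with recall stated as days 31-60. Add the same questions in both arms at the existing in-person day-30 visit, before any advice is given, with recall of days 1-30. State this under Measurement Time Points, Exploratory Outcomes and Behavioral Factor Assessment. Use only the pre-advice values to describe imbalance or effect modification. Report the day-60 values and the change from day 30 as post-intervention data or a possible mechanism.

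Most participants are probably past that visit. Recruitment ended in July 2025, and with a latest end date of December 31, 2025, the last day-30 visit falls at about December 1, 2025. For participants past day 30, stop calling the day-60 values confounders, report them descriptively by arm as post-randomisation data, do not stratify or adjust the effect on them, and carry the pre-advice assessment into the definitive trial.

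The cost is a few minutes per participant still to reach day 30, and an amendment reviewed by the ethics committee as described under Protocol Amendments. No extra visit is needed. The fallback needs only changes in wording and reporting.

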### Instruments

#### Commercial-Grade Wearables

The study uses Samsung Galaxy Watch 4 [27] for sleep tracking. Samsung Galaxy Watch 4 has been selected following a systematic evaluation of available consumer sleep tracking devices. The selection criteria are as follows: validation evidence (published PSG comparison studies), parameter comprehensiveness (10 sleep variables vs 3‐5 in most competitors), data accessibility for research use, cost feasibility (US $200‐250 per unit [within budget]), operationalization of sleep quality through a composite sleep score (scale 1-100) that algorithmically integrates multiple dimensions, and user compliance factors (battery life >24 hours). While alternatives exist (Fitbit: limited architecture data; Apple Watch: iOS requirement; Garmin: higher cost; WHOOP: subscription model), Samsung Galaxy Watch 4 provides an optimal balance of scientific validity, data richness, and practical feasibility for this pilot study [29,30,36-43,71,105-107].

This sleep monitoring system is noninvasive, involves ambulatory or home-based deployment, is contact-based (wrist-worn), has comprehensive architecture analysis parameters, involves real-time analysis, and is a consumer-grade device with clinical validation studies. The sensors include an accelerometer, a gyroscope, a photoplethysmography sensor, a bioelectrical impedance sensor, and an ambient light sensor [27,121]. This positioning offers ecological validity while acknowledging trade-offs in precision compared with laboratory approaches.

#### Pairing Devices

Mobile phones (1 per wearable) are used for data synchronization.

#### PSQI Questionnaire

The PSQI is used for evaluation. It is a validated subjective sleep quality assessment [28].

#### Computer

The researcher’s computer is used for data storage, processing, and ML analysis.

### Study Timeline

The overall experimentation period is 15 months (all volunteers). The start date is October 4, 2024, and the maximum end date is December 31, 2025. The experiment duration for each volunteer is 60 days.

### Artificial Intelligence Accountability and Algorithmic Governance

This study uses ML algorithms to analyze participant sleep data and generate personalized recommendations. The governance framework is presented below.

#### Algorithmic Transparency Obligations

##### Participant Information

The participant information aspects are as follows:

Informed consent explicitly states the use of ML for sleep data.Participants are informed that recommendations represent statistical pattern recognition, not clinical judgment.Models identify correlations, not causation.Recommendations are behavioral suggestions, not medical advice.Participants maintain full autonomy to accept, modify, or ignore recommendations.

##### Explainability

The explainability aspects are as follows:

ML recommendations are accompanied by plain-language explanations.SHAP visualizations show which sleep parameters influence the individual model.Example: “Your model identified REM sleep and sleep timing consistency as your two strongest predictors. When you had ≥90 minutes REM and went to bed within 30 minutes of your average time, your scores were typically 8‐12 points higher.”

##### Human Oversight

The human oversight aspects are as follows:

ML models suggest recommendations, but the principal researcher reviews all outputs before delivery.The human-in-the-loop approach ensures recommendations are safe, coherent, and appropriate.Models do not make automated health decisions.

### Participant Rights Concerning Algorithmic Outputs

Participant rights are as follows:

Right to explanation: Participants may request a detailed explanation of how personalized recommendations are generated.Right to question: Participants may challenge recommendations they believe are inaccurate or inappropriate. The researcher is available for discussion and can modify recommendations based on participant feedback.Right to decline: Participants may decline to implement some or all ML-derived recommendations without penalty or withdrawal from the study. Nonadherence is tracked but does not affect participant standing.Right to human review: Participants may request that the principal researcher personally review their data and provide alternative recommendations if dissatisfied with ML outputs.Access to model information: Participants may request information about ML methodology (algorithms used, training process, and validation approach) in plain language.

### Data Retention and Security for ML Processes

The data retention and security aspects are as follows:

Raw sleep data: Data from 1920 nights are stored encrypted on the researcher’s local computer with password protection and backup. The data are retained for 5 years after publication and are then securely destroyed.ML model files: Individual participant models (random forest and XGBoost) are stored on the researcher’s local computer separately from identifiable data. Models contain learned patterns but no raw data. The information is retained indefinitely for reproducibility verification. The information can be deleted upon participant request during the identifiable data retention period.SHAP values and feature importance rankings: The data are stored as CSV files on the researcher’s local computer, linking Participant_ID to rank predictive features. These data have the same retention schedule as the raw data (5 years after publication).Transmission security: No ML processing occurs on participant devices or cloud services. All analyses are conducted on the researcher’s local computer. No data are transmitted to third parties or commercial ML platforms.

### Accountability Framework

The accountability framework involves the following aspects:

Adverse events from artificial intelligence (AI): If ML-derived recommendations cause participant harm (eg, a recommendation to reduce sleep duration leads to excessive daytime sleepiness affecting work safety), the event is documented as an adverse event. The researcher notifies the ethics committee, and an investigation is conducted to determine if a systematic model error exists.Replication and audit: The ML code, trained models, and analysis scripts are made available to the ethics committee and peer reviewers upon request.Model performance monitoring: During the study, the principal researcher monitors whether the experimental group shows unexpected negative outcomes (eg, worsening sleep scores), triggering a review of ML recommendation patterns for systematic errors.

### Compliance With AI Governance Frameworks

This study follows the principles from the World Health Organization (WHO) guidance on ethics and governance of AI for health (transparency, accountability, and human oversight) and the International Association of Scientific, Technical & Medical Publishers recommendations for AI use in academic manuscript preparation [122].

### Ethical Considerations

#### Research Ethics Approval

This research has been reviewed and approved by the Institutional Committee on Research Ethics of Tecnológico de Monterrey (ethics approval number: CA-EIC-2408-06; approval date: October 2024; review type: full committee review). The study complies with the principles of the Declaration of Helsinki for medical research involving human participants and the international ethical guidelines for health research. There is no compensation for participation in the study.

#### Protocol Amendments

Any modifications to the eligibility criteria, interventions, outcomes, or ethical procedures will be submitted to the ethics committee for review and approval prior to implementation. Amendments will be documented in protocol version history with the rationale for changes.

#### Informed Consent Collection

The principal researcher has completed ethical training to obtain informed consent from potential trial participants.

#### Additional Consent Provisions for the Collection and Use of Participant Data and Biological Specimens in Ancillary Studies

It is not applicable to consider additional consent provisions for the collection and use of participant data and biological specimens in ancillary studies since there are no additional studies.

#### Confidentiality: Data Protection

Personal data are not shared. The data are only used to allocate participants to the study groups and to ensure consistent assignment of the proper Participant_ID to keep the process accurate and deidentified. The participants can access their personal data or request data correction. Data are protected before, during, and after the trial.

#### Compensation for Research-Related Injury

In the unlikely event of research-related injury, immediate medical care coordination will be provided by the researcher, participants can use existing health insurance for treatment, no additional compensation will be provided, and the incident will be documented and reported to the ethics committee. The anticipated risk is minimal (behavioral intervention, noninvasive device use, skin irritation from the device, sleep tracking anxiety, and time commitment).

### Ancillary and Posttrial Care

#### Incidental Findings

Participants with incidental findings during the study may be withdrawn and referred for severe sleep deterioration (sleep score <30 for >1 consecutive week). Participants may be withdrawn from the study and referred to sleep medicine services at their medical institutions. Contact information may be provided for sleep specialists in Mexico City. There are no study-related costs for referral (participants use existing health insurance).

